#### Data collection

All patients in the study sample will be invited to complete a self-report questionnaire (Additional file 1). The questionnaire will include validated measures for assessing different aspects of emotional distress, and adjustment to emotional stressors, in combination with additional questions about emotional support and intervention use. We have deliberately chosen short validated measures, which together with the additional questions, should not take longer than 20 min to complete and avoid over-burdening patients.

#### Measures employed in the study and rationale

***Validated measures***

The Distress Thermometer (DT) [60] has been selected as the primary measure of distress for this study; and will be used to enable comparisons of the level of distress at different stages in the ESRD pathway and how support needs vary at different levels of distress. There are few validated tools for measuring emotional and psychological needs at the lower-level among ESRD patients, or chronic disease patients in general. Existing studies have tended to use validated tools designed to measure anxiety and depression e.g. the Hospital Anxiety and Depression Score (HADS), the Beck Depression Inventory (BDI, BDI-1A, BDI-11), looking for scores below the thresholds set for detecting the clinical presence of anxiety or depression. An advantage of these tools is that they are reliable measures, validated for use with renal patients. However, they appear to restrict lower-level emotional issues to those linked with low-level anxiety and depression, and therefore, are not suitable for this study which uses a broader definition, encompassing a range of symptoms, emotions and experiences associated more with distress (see Background).

There are two main tools which have been developed to measure distress: the Brief Symptom Inventory (BSI) and the more recently designed DT. The DT is a measure of global distress initially developed by Roth et al. [60] for the National Comprehensive Cancer Network (NCCN). The term ‘distress’ was chosen by NCCN because it is “more acceptable and less stigmatizing than ‘psychiatric’, ‘psychosocial’ or ‘emotional’, sounds ‘normal’ and less embarrassing, and can be measured by self-report” [61]. Although developed for cancer patients, the DT has been validated for use in a range of chronic disease populations, including more recently a UK renal population [62]. Furthermore, being a visual measure makes the DT particularly helpful for people with language difficulties [39].

In cancer populations, a score of 4 or 5 (on a 0–10 scale) on the DT is defined as mild distress, a score of 6 or 7 as moderate distress, and 8 or higher as severe distress [63]. For this study, we will classify ESRD patients who score between 4 and 7 on the DT as having lower-level emotional and psychological problems. A problem list accompanies the DT to identify causes for distress and this will also be included in the study questionnaire.

We will use the DT contained within the Emotion Thermometers (ET) [63, 64]. The ET is a simple five-domain visual analogue scale. Each domain is self-rated on an 11-point (0 to 10) Likert scale. In addition to the Distress Thermometer, it contains the Anxiety, Depression, Anger, and Help Thermometers. Patients score these thermometers on the basis of how much emotional upset they have experienced during the preceding week, including the present day. Containing a combination of items, the ET has been found with cancer patients to be more accurate than a single domain for the identification of any significant emotional difficulty, as well as the assessment of broadly defined distress; 51 % of patients who scored below the cut-off point for distress using the DT recorded emotional difficulties on the ET [64]. Furthermore, the ET is very quick to complete (less than one minute) with non-completion rates low in comparison with conventional measures [63, 64].

The Positive and Negative Affect Schedule [PANAS] will be used to measure patients’ adjustment to emotional stressors. Developed and validated by Watson et al. [32], this 20-item instrument that measures positive and negative affect has been widely used in different chronic disease populations and some renal populations [65]. Positive Affect (PA) reflects the extent to which a patient feels enthusiastic, active and alert, while the Negative Affect (NA) dimension assesses subjective distress and discomfort. PA and NA have high internal consistency and are largely uncorrelated [32].

Each item of the PANAS is rated on a 5-point scale to indicate the extent to which the respondent has felt this way in general or a specific time-period such as ‘in the past few hours’ or ‘during the past week’. We will use a time period of ‘during the last week’.b)***Additional measures***

Patients’ perceptions and views will also be measured on: recent events that have caused distress; ability to cope with their illness and treatment; extent to which feel supported by renal staff; interventions used for distress; benefits and satisfaction from receiving support for distress from renal staff; practical ideas about future support for distress.

Most of these questions will have pre-set answer options using an 11-point (0–10) Likert response scale [66]. Negatively and positively worded answer options will be balanced to avoid ‘yea’ saying’. An open-ended question at the end will allow free-text responses, to avoid missing any types of support considered important through use of pre-set answer options. Tick-box data will be collected on age, gender, ethnicity, relationship status, length of time since diagnosis, length of time on dialysis or with a functioning renal transplant, and dialysis treatment type. Patients will also be asked whether they received any assistance in completing the questionnaire. Additionally, respondents will be asked if they are willing to participate in a further individual telephone or face-to-face interview, and if so to provide their contact details.

#### Sample size calculation

The sample size calculation – based on the study objective to determine whether there are any differences in distress at different stages of the ESRD pathway - assumes a 1.5-point difference on the DT between patient groups (pathway stages) with the largest and smallest means. A two-sided alpha of 0.05 and 90 % power have been used. This gives an effect size, f, of 0.20. A sample size calculation (using G*Power version 3.1.9.2) gives a total sample size of 485, approximately 97 in each patient group across the two study sites. Since group sizes will not be equal, ideally this would be the sample size requirement for the smallest group, although it is noted that this may not be met in practice for all groups (see Table 1).

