### Participants

Patients at five different points across the ESRD pathway, and renal staff working with them, will be studied. Existing evidence, and discussion with clinicians in the study sites, indicates that ESRD patients are likely to experience different types and levels of distress at five key stages of the pathway. The five stages are (1) diagnosed with chronic kidney disease (CKD) stage 5 and still pre-RRT; (2) on dialysis (peritoneal dialysis [PD], haemodialysis [HD], or HHD) for less than 2 years, and not on the transplant list; (3) on dialysis for more than 2 years, and not on the transplant list; (4) on dialysis and on the transplant list; and (5) with functioning transplant.

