#### Analysis

One-way ANOVA will be used to analyse data from the DT, ET, and PANAS, combining data across both sites. If there is a statistical significant difference on the main analysis measure, the DT, between patients at different stages on the ESRD pathway, then appropriate post-hoc t-tests to compare individual patient groups will be undertaken, with *p*-values corrected for multiple comparisons using the Bonferroni Adjustment. Comparisons of scores between patient groups and study sites will be made using two-way ANOVA, although we may not have sufficient power to detect small differences between sites.

The remaining questionnaire data, although on Likert scales, will initially be analysed as continuous data, using means and standard deviations or medians and inter-quartile ranges as appropriate for the distribution. Scores from individual items in each question-group will be summed prior to analysis e.g. to give a composite ‘coping’ score. Appropriate corrections for multiple comparisons will be made given that multiple questions are being asked.

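### The stated effect size, power and sample size do not agree: f = 0.20 at 90% power needs 390 patients, and 485 is the answer for f = 0.18

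*Protocol article*

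**What the plan says.** The section "Sample size calculation" (Study 1, Quantitative data) builds the calculation on the Distress Thermometer (DT). It "assumes a 1.5-point difference on the DT between patient groups (pathway stages) with the largest and smallest means". It then says "A two-sided alpha of 0.05 and 90 % power have been used" and "This gives an effect size, f, of 0.20", and reports that the software "gives a total sample size of 485, approximately 97 in each patient group across the two study sites". It treats the per-group figure as the ideal size for the smallest group and concedes, pointing to Table 1, that some groups may not reach it.

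Two other sections fix the remaining inputs. "Participants" defines five pathway stages. The Study 1 "Analysis" section states the test: "One-way ANOVA will be used to analyse data from the DT, ET, and PANAS, combining data across both sites".

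**The concern.** Once f, alpha, power and the number of groups are stated, the total for a one-way ANOVA is determined. No standard deviation is needed. The printed inputs do not lead to the printed total, so at least one figure is wrong.

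This is the only sample size calculation in the article, and it supports the first Study 1 objective, on differences in distress between pathway stages. It also supplies the benchmark of 97 per group against which the expected returns in Table 1 are to be read. If the benchmark rests on a slip, the reader cannot say which stages are too small, or what power the study has at the returns it expects.

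**Working it through.** **Inputs**

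- Five groups: "Participants".
- One-way ANOVA, sites combined: Study 1 "Analysis".
- Alpha 0.05, power 90%, f = 0.20, total 485 (97 per group), 1.5-point range of means: "Sample size calculation".
- Expected returns of 144, 90, 189, 65 and 145, total 633: Table 1.

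**Formula.** For k equal groups and total N, the F statistic has k − 1 = 4 and N − 5 degrees of freedom and noncentrality λ = N·f². Power is the probability that this noncentral F exceeds the central 95% point. The required N is the smallest multiple of 5 with power of at least 0.90.

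**Attempt to reproduce 485**

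| f | N | λ = N·f² | Power |
|---|---|---|---|
| 0.20 | 385 | 15.40 | 0.896 |
| 0.20 | 390 | 15.60 | 0.900 |
| 0.20 | 485 | 19.40 | 0.957 |
| 0.18 | 480 | 15.55 | 0.8998 |
| 0.18 | 485 | 15.71 | 0.903 |

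The stated inputs give 390, or 390/5 = 78 per group. The gap is 485 − 390 = 95 patients, and 485/390 = 1.24. Changing f to 0.18, and nothing else, gives 485 exactly.

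**Other explanations tried**

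- Rounding of f: 0.195, the smallest value that rounds to 0.20, needs 410.
- Smaller alpha at f = 0.20: 0.025 gives 450 and 0.01 gives 530.
- Higher power at f = 0.20: 95% gives 470 and 96% gives 495.
- A two-way layout with ten cells: 390 with 4 numerator degrees of freedom, 505 with 9.
- Inflation for 20% loss: 390/0.80 = 487.5, so 488. The article states no such inflation, and its 40% response rate is applied separately in Table 1.

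None returns 485.

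**Does the 1.5-point difference settle it?** It does not, because f is the SD of the group means divided by the within-group SD, and the article gives neither the within-group SD nor the position of the middle groups. Two patterns, assumed for illustration:

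- Two groups at the extremes and three midway: SD of means = 1.5 × √(1/10) = 0.474. Then f = 0.20 implies a within-group SD of 0.474/0.20 = 2.37, and f = 0.18 implies 0.474/0.18 = 2.64.
- Evenly spaced means: SD of means = 1.5 × √(1/8) = 0.530. Then f = 0.20 implies 2.65, and f = 0.18 implies 2.95.

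An SD of about 2.65 therefore fits f = 0.20 under one pattern and f = 0.18 under the other.

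**Effect on the benchmark**

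| Stage (expected returns) | Against 78 | Against 97 |
|---|---|---|
| On dialysis under 2 years, not listed (90) | meets | misses |
| On dialysis and listed (65) | misses | misses |
| The other three (144, 189, 145) | meet | meet |

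**Effect on power at the Table 1 returns.** With unequal groups, λ = Σ nᵢ(mᵢ − m̄)²/SD², where m̄ is the weighted mean. Take the two-extremes pattern in its least favourable placement, with the groups of 90 and 65 at −0.75 and +0.75:

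- Σ nᵢmᵢ² = 155 × 0.5625 = 87.19.
- m̄ = 0.75 × (65 − 90)/633 = −0.0296, so 633 × m̄² = 0.56.
- The difference is 86.63.
- SD 2.37: λ = 86.63/5.617 = 15.42, power about 90%.
- SD 2.64: λ = 86.63/6.970 = 12.43, power about 81%.

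With evenly spaced means, the least favourable placement gives about 94% at SD 2.65 and 88% at SD 2.95.

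**The case against.** The strongest reply is that nothing in the conduct of the study depends on 485. Every eligible patient at both sites is invited (743 + 838 = 1,581), and the 633 expected returns exceed both 390 and 485. If f = 0.20 is right, the slip is conservative. If f = 0.18 is right, then 485 at 90% power is already correct and only one printed decimal is wrong. The article also calls the per-group figure an ideal and admits that some groups may not reach it. The low power of about 81% arises only if the two smallest stages are the two extremes and the rest sit in the middle; in the best placement of that pattern, power exceeds 99% at either SD. Finally, a condensed article may leave the SD and the pattern of means to the full protocol.

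Most of this stands. Recruitment does not change, and with equal groups 485 does not fall short of 90% under either reading. It does not remove the contradiction: the three figures are printed together and cannot all hold. Omitting the SD from an article would not by itself be an error. It matters here because, without it, the reader cannot find the wrong figure.

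**Conclusion.** The concern holds: the paragraph is wrong as written. With five equal groups and alpha 0.05, either the total is 390 for f = 0.20 at 90% power, or f is 0.18 for 485 at 90%, or power is 95.7% for f = 0.20 at 485. This conclusion needs only the stated inputs and the standard noncentral-F calculation.

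That f is the misprinted figure is an inference from the exact match at 0.18; the article does not establish it. The consequence is limited but real. The benchmark is 78 or 97 per group, and the status of the stage with 90 expected returns turns on which. In the worst case under the two-extremes pattern, power at the expected returns is about 90% or about 81%. Those last two figures rest on the assumed pattern of means and on SDs inferred from f, not on values given in the article.

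**What to change.** Return to the G*Power output and make the three figures agree, in whichever form matches the calculation actually run:

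- f = 0.18, total 485 (97 per group), 90% power;
- f = 0.20, total 390 (78 per group), 90% power; or
- f = 0.20, total 485 (97 per group), 96% power.

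Add the DT standard deviation and the pattern of group means that turn 1.5 points into f. Then restate which Table 1 stages are expected to miss the per-group figure: one stage if it is 78, two if it is 97.

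The cost is a sentence or two of text. Invitations, analysis and patient numbers stay as they are.

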#### Analysis

One-way ANOVA will be used to analyse data from the DT, ET, and PANAS, combining data across both sites. If there is a statistical significant difference on the main analysis measure, the DT, between patients at different stages on the ESRD pathway, then appropriate post-hoc t-tests to compare individual patient groups will be undertaken, with *p*-values corrected for multiple comparisons using the Bonferroni Adjustment. Comparisons of scores between patient groups and study sites will be made using two-way ANOVA, although we may not have sufficient power to detect small differences between sites.

The remaining questionnaire data, although on Likert scales, will initially be analysed as continuous data, using means and standard deviations or medians and inter-quartile ranges as appropriate for the distribution. Scores from individual items in each question-group will be summed prior to analysis e.g. to give a composite ‘coping’ score. Appropriate corrections for multiple comparisons will be made given that multiple questions are being asked.

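### Study 1 compares distress across pathway stages without adjustment, and no named quantitative analysis uses the age, gender and ethnicity collected, so it cannot separate stage from type of patient

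*Protocol article*

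**What the plan says.** The Analysis section under Study 1, Quantitative data, names these methods:

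- Main comparison: "One-way ANOVA will be used to analyse data from the DT, ET, and PANAS, combining data across both sites".
- If the DT result is significant, "appropriate post-hoc t-tests to compare individual patient groups will be undertaken", with Bonferroni correction.
- Site: "Comparisons of scores between patient groups and study sites will be made using two-way ANOVA".
- Remaining questionnaire items: summed into composite scores and treated as continuous, "using means and standard deviations or medians and inter-quartile ranges as appropriate for the distribution". The section adds: "Appropriate corrections for multiple comparisons will be made given that multiple questions are being asked".

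On data collected, the account of the additional measures says "Tick-box data will be collected on age, gender, ethnicity, relationship status, length of time since diagnosis", and goes on to "length of time on dialysis or with a functioning renal transplant, and dialysis treatment type". Site is known from the code on the reply envelope.

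On purpose, Aims and objectives sets out to establish what support is needed, when, and by which patients. The first objective concerns distress by pathway point. The third concerns patient groups that need and want more support than others. The measures section adds that the DT will show "how support needs vary at different levels of distress".

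**The concern.** The five stages are defined by treatment, transplant listing and time on dialysis. Patients are not randomised to them, so the stages may differ in age, ethnicity and other characteristics. If they do, a difference in mean DT between stages mixes the experience of being at that stage with the kind of patient who is there.

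The results are meant to guide where and to whom low-cost interventions are directed. Local context separates the patients in greatest need from the points on the pathway where effect would be strongest. Staff attitudes and behaviour says cultural and ethnic background may be critical. Deciding between targeting a stage and targeting a type of patient needs an analysis that contains both, and none is named.

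A second, smaller matter is that the expected group sizes are very unequal. The usual ANOVA F test pools variances, and its error rate at such sizes is sensitive to unequal spread.

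**Working it through.** **1. Which question has which analysis**

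| Question posed | Named quantitative analysis |
|---|---|
| Distress by stage (objective 1) | One-way ANOVA, post-hoc t-tests |
| Stage and site | Two-way ANOVA |
| Support by stage | Composite scores; corrections promised, model not named |
| Need by age, gender or ethnicity (aim; objective 3 if read beyond stage) | None |
| Support needs by level of distress | None |

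**2. Expected group sizes (Table 1)**

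At a 40% response: 0.4 × 360 = 144; 0.4 × 225 = 90; 0.4 × 472 = 188.8, so 189; 0.4 × 162 = 64.8, so 65; 0.4 × 362 = 144.8, so 145. The rounded total is 633, as in the table. Largest to smallest is 189/65 = 2.9.

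**3. Size of possible confounding by age (all inputs assumed)**

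The article gives neither age by stage nor a slope of DT on age.

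Shift in a stage contrast = age gap in decades × DT change per decade.

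- Low: 1.0 × 0.2 = 0.2 points; 0.2/1.5 = 13% of the design difference.
- High: 1.5 × 0.4 = 0.6 points; 0.6/1.5 = 40%.

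Next, the chance that the crude test is significant when stage itself has no effect. Assume stages 1 to 3 are older than stages 4 and 5. Take SD 2.65, the value implied by f = 0.20 and a 1.5-point range if the five means are equally spaced (SD of means 0.530; 0.530/0.20 = 2.65).

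Worked case, 0.3 points per decade and a 10-year gap: stages 1 to 3 hold 423/633 = 0.668 of respondents. The SD of the means is 0.3 × √(0.668 × 0.332) = 0.141, so f = 0.141/2.65 = 0.053. The noncentral F test (4 and 628 df, N = 633) is then significant 16% of the time.

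| DT per decade | Age gap | Chance of a significant stage test |
|---|---|---|
| 0.2 | 5 years | 6% |
| 0.3 | 10 years | 16% |
| 0.5 | 10 years | 39% |
| 0.5 | 15 years | 77% |

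The range is wide because the inputs are unknown.

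**4. Site as a source of mixing**

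Site 2's share by stage is 180/360 = 50%, 111/225 = 49%, 259/472 = 55%, 106/162 = 65% and 182/362 = 50%. With equal response rates, an assumed 1-point DT difference between sites moves a stage contrast by at most 0.654 − 0.493 = 0.16 points, or 0.16/1.5 = 11% of the design difference. Site matters little here, and the two-way ANOVA already contains it.

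**5. Error rate at the Table 1 sizes**

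10,000 simulated data sets per row, normal data, equal means, n = 144/90/189/65/145. SDs are assumed and listed in stage order. The simulation standard error is about √(0.05 × 0.95/10,000) = 0.2 percentage points.

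| SDs | Classical ANOVA | Welch |
|---|---|---|
| Equal | 5.1% | 5.1% |
| 2.6, 2.9, 2.3, 3.1, 2.6 | 7.1% | 5.0% |
| 2.6, 2.9, 2.2, 3.2, 2.6 | 7.6% | 4.6% |
| 2.7, 3.0, 2.5, 3.5, 2.7 | 7.8% | 4.9% |
| 2.5, 3.0, 2.0, 4.0, 2.5 (extreme) | 11.5% | 4.7% |
| 2.6, 2.3, 3.1, 2.2, 2.6 | 3.3% | 4.8% |

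The test is liberal when the small groups vary more, conservative when they vary less, and correct when spreads are equal.

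**6. Cost of adjustment in power**

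At f = 0.20 and N = 633, power is 99.0% with no covariates and 99.0% after spending ten degrees of freedom on them.

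**The case against.** **The crude contrast fits objective 1.** A service choosing where to screen needs the distress of the patients actually at each stage, whatever their age. The article makes no causal claim about stage. This stands: a reader might infer that the unadjusted ANOVA is the wrong primary analysis, and the text does not support that. The adjusted model belongs beside it, because it answers a different question.

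**Site is already handled.** This stands. A reader might list site among the unused variables, but the planned two-way ANOVA includes it.

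**Objective 3 is not left without any analysis.** The sample size section equates patient groups with pathway stages, composite scores are planned, and interviewees are sampled for diversity of age, gender and ethnicity. So it would be wrong to say the objective has no analysis. But the Study 1 aim asks separately when and by which patients support is needed, and objectives 1 and 4 already cover pathway points. The interviews cannot estimate differences between patient types: they are purposive, five per stage per site, and restricted to respondents scoring 4 to 7 on the DT, or below 4 on the DT with 4 to 7 on another thermometer.

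**Equal variances are never stated.** Correct. The pooled form is inferred from the word ANOVA, and the form of the t-tests is left open. Variance checks and covariate lists may also sit in a fuller document not shown. This limits the point to an improvement on the methods the article names.

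**Dialysis type cannot be a general covariate.** This stands. It does not exist for pre-dialysis patients and is not a current treatment after transplant, and time on dialysis separates stage 2 from stage 3.

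**Bonferroni is valid.** It is. Holm is a small gain in power and corrects no error.

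**Conclusion.** The point holds in limited form. The named stage comparison is unadjusted for patient characteristics. Age, gender and ethnicity are collected but enter no named quantitative analysis, and none is named for how support needs vary with distress. The plan can therefore say where distress is higher, but not whether that reflects the stage or the patients at it.

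The documents do not fix the size of the problem. The 0.2 to 0.6-point shift and the 6% to 77% range rest on assumed age gaps, slopes and SD. The error rates away from 5% rest on assumed unequal SDs. A reader might conclude that the planned test has an inflated error rate. That is not shown: with equal SDs it holds its level, and in one plausible direction it is conservative.

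This is a worthwhile, inexpensive strengthening of the analysis. It does not invalidate the planned one.

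**What to change.** 1. Keep the crude stage means and the omnibus comparison as the answer to objective 1. Use Welch's ANOVA and unequal-variance t-tests, with Holm in place of Bonferroni for the ten pairwise contrasts (5 × 4/2).
2. Add a prespecified secondary linear model of DT on stage, site, age, gender and ethnicity, with heteroscedasticity-robust standard errors. Report it beside the crude means.
3. For objective 3, apply the same model to the support scores, with DT level as a further predictor. This also supplies the missing analysis of support needs by level of distress. State whether patient groups in that objective means stages, patient characteristics or both.
4. Use dialysis type and time on dialysis only in a model confined to the dialysis stages (2 to 4).

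The cost is analysis wording and a little more analysis; every variable is already collected. Respondents with missing tick-box answers must be imputed or dropped from the adjusted models, and the plan should say which.

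### Bonferroni after a significant F test is valid for the stage comparisons on the Distress Thermometer but needlessly conservative; Holm over the same t-tests is a free improvement

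*Protocol article*

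**What the plan says.** The Participants section defines the groups: "Patients at five different points across the ESRD pathway". The Study 1 Analysis section plans a one-way ANOVA across these stages. The pairwise step is conditional: "If there is a statistical significant difference on the main analysis measure, the DT" is found between stages, post-hoc t-tests follow, with p-values "corrected for multiple comparisons using the Bonferroni Adjustment". Neither the pairs nor their number is given.

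The Sample size calculation section "assumes a 1.5-point difference on the DT between patient groups (pathway stages) with the largest and smallest means". It uses "A two-sided alpha of 0.05", and "90 % power have been used". That power belongs to the overall test, not to any pair. No SD is printed. Table 1 (Setting) expects 144, 90, 189, 65 and 145 responses at a 40% response rate.

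**The concern.** The F test can show that the stages differ somewhere; only the pairwise comparisons show which. One of Study 1's objectives is to explore at which points in the pathway patients should be screened and offered support, and these comparisons feed that question. They are also where the design is thinnest: two stages are expected to return 90 and 65 questionnaires, below the 97 per group aimed for. All eligible patients at the two sites are already to be invited, so the sample there cannot easily be enlarged. A correction that leaves part of the 5% error allowance unused therefore gives up power that could be had at no cost.

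**Working it through.** **The plan's own figure.** The article gives no power figure for the pairwise tests. Its one figure is for the overall test: it "gives a total sample size of 485, approximately 97 in each patient group across the two study sites" from f = 0.20. A noncentral F calculation (5 groups, alpha 0.05, noncentrality N·f²) does not return this: f = 0.20 needs N = 390, and 485 matches f = 0.18. That is a separate matter and does not alter the ranking of the methods, but it helps to bracket the missing SD.

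**SD (assumption).** Put the two extreme stages 1.5 points apart and the other three midway. The between-stage SD is √[(0.75² + 0.75²)/5] = 0.474. Then f = 0.20 implies SD = 0.474/0.20 = 2.37, and f = 0.18 implies 0.474/0.18 = 2.635. The range used is 2.37 to 2.65.

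**Number of pairs (inference).** Five stages give 5 × 4/2 = 10 pairs, so Bonferroni tests each at 0.05/10 = 0.005. With the Table 1 sizes (total 633, 628 df) the critical |t| is 2.817.

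**Why Holm never rejects less.** Holm orders the m p-values and compares the smallest with 0.05/m, the next with 0.05/(m − 1), and so on up to 0.05, stopping at the first failure. No threshold is below 0.05/m, so every Bonferroni rejection stands, whatever m is. It holds family-wise error at 5% under the same assumptions, without a prior F test. Its first step is Bonferroni's, so it adds nothing to the chance of a first rejection; the gain comes in later pairs.

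**Family-wise error with no true differences** (simulation, Table 1 sizes, ten pairs, pooled variance):

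| Procedure | Family-wise error |
|---|---|
| Bonferroni after a significant F (the plan) | 3.4% |
| Holm, no F condition | 3.9% |
| Tukey-Kramer, no F condition | 4.9% |

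**Power for the 90 v 65 pair, 1.5 points apart.** Check by hand: √(1/90 + 1/65) = 0.1628. At SD 2.65 the noncentrality is 1.5/(2.65 × 0.1628) = 3.48, so Bonferroni without the F condition has power of about Φ(3.48 − 2.817) = 75%. At SD 2.37 it is 1.5/(2.37 × 0.1628) = 3.89, and Φ(3.89 − 2.817) = 86%. The simulation agrees and adds the F condition and the other methods:

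| Pattern of means | SD | Plan | Holm, no F condition | Gain with Holm | Tukey-Kramer, no F condition |
|---|---|---|---|---|---|
| Only these two stages extreme | 2.37 | 84.8% | 86.2% | 1.4 | 87.6% |
| Only these two stages extreme | 2.65 | 73.3% | 75.1% | 1.8 | 77.1% |
| Two clusters (two stages v three) | 2.37 | 85.8% | 90.1% | 4.3 | 87.6% |
| Two clusters (two stages v three) | 2.65 | 74.5% | 80.8% | 6.3 | 77.1% |

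**What the F condition costs.** In the two-extremes pattern it takes about 1.0 (SD 2.37) to 1.3 points (SD 2.65) from this pair. In the two-cluster pattern it takes nothing, because the F test is almost always significant. Dropping it raises the chance of finding at least one true difference by about 1 to 1.6 points in the two-extremes pattern (78.4% to 80.0% at SD 2.635).

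**When Tukey-Kramer helps.** Its critical |t| is 2.736. Bonferroni's is 2.817 for ten pairs and 2.744 for eight, but 2.699 for seven. With seven or fewer planned pairs Tukey-Kramer is less powerful than Bonferroni.

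**The case against.** The strongest reply is that nothing here is wrong. The procedure is stated in advance, familiar and conservative, and contradicts nothing else in the article. The sample size was set for the overall test, and the article concedes that the smaller groups may fall short. This stands: the point concerns efficiency only.

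Four stronger readings are tempting, and the article does not support them.

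- *The plan tests ten pairs at 0.005 each.* The text does not list the pairs, so ten is an inference.
- *The plan is dominated by both Holm and Tukey-Kramer.* That is unconditional only for Holm, and only in the sense of never rejecting less. Tukey-Kramer needs about eight or more pairs to beat Bonferroni.
- *About 6 points of power are being lost.* That size arises only with Holm, in the two-cluster pattern, at the larger SD. That pattern has a between-stage SD of 1.5 × √(0.4 × 0.6) = 0.735, so f = 0.735/2.65 = 0.28, well above the planning value of 0.20. In the two-extremes pattern, which underlies the SD range, the gain is 1 to 2 points.
- *These tests decide where support is targeted.* Under Overview of design, the questionnaire results are combined with interviews and staff data. The pairwise tests inform the answer but do not settle it.

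It can also be said for the F condition that, without it, the F test and the pairwise tests become two routes to a false claim. With no true differences, the chance that either rejects is about 5.0% + 3.9% − 3.4% = 5.5%. That matters only if the overall and pairwise tests are treated as one family. The family-wise error of the pairwise statements stays below 5% either way.

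**Conclusion.** The concern holds as a minor, optional improvement. The planned correction is valid, and a reader should not infer that error control fails or that results under it would be unsound. It leaves part of the 5% allowance unused (about 3.4% spent, if ten pairs are tested), and Holm does at least as well for any number of pairs. The size is modest: for the 90 v 65 pair, about 1 to 2 points of power if only those stages are extreme, and about 4 to 6 points if the stages form two clusters. There is no gain in finding at least one difference beyond the 1 to 1.6 points from dropping the F condition. That Holm never rejects less is a mathematical fact. The power figures rest on ten pairs, an assumed SD of 2.37 to 2.65, a common variance, approximate normality of the mean scores, and the Table 1 response numbers.

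**What to change.** In the Study 1 Analysis section, replace the Bonferroni correction by Holm-adjusted p-values over the planned pairwise t-tests, and do not make those tests conditional on the F test. State which pairs are planned (all ten, if that is the intention). The ANOVA can stay as the overall test of whether the stages differ.

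The cost is a few words in one section, with no new data and no change in sample size. Holm does not yield simple simultaneous confidence intervals, but the section mentions only corrected p-values, so nothing now promised is lost. If simultaneous intervals are wanted and all ten pairs are compared, Tukey-Kramer is an alternative; with about seven or fewer pairs it should not be used in place of Bonferroni or Holm. If the team prefers to keep the F condition so that the overall and pairwise tests count as one family, Holm can be applied behind it and is still never worse than the present plan.
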